**Methods:**

The objective of the current pilot study is to explore the feasibility of a trial investigating the impact of computerized cognitive training, yoga, and an active control intervention (wellness education) in individuals with aMCI by conducting a group-randomized, multisite, parallel, three-arm pilot study. We will establish preliminary effect sizes regarding the association of each intervention with neuroimaging and cognitive and participant-reported measures. We also aim to estimate the strength of association between the various outcomes. The current trial aims to recruit 75 people with aMCI and their 75 cognitively healthy care partners through clinics and senior care facilities. The initial intervention will last 10 days and will consist of 1 h daily of the assigned intervention i.e., (yoga, computerized cognitive training, or wellness education) combined with 1 h of memory compensation training and 1 h of support groups. Twenty-five participants will be group-randomized to each arm using a random number generator. Study staff and participants will be kept blind until recruitment is complete for each group. After the initial two-week intervention, participants will continue the assigned intervention for 24 weeks. Outcome measures are: functional connectivity and cerebral perfusion as assessed by magnetic resonance imaging; cognition; daily functioning; mood; anxiety; self-efficacy; caregiver burden; quality of life; and study feasibility including recruitment and retention rates.

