### Trial objectives and hypotheses

The primary aims of this pilot are:

#### Aim 1

To conduct a preliminary examination of the impact of computerized cognitive training, yoga, and an active control intervention (wellness education) on changes in cerebral perfusion and functional connectivity, as measured by magnetic resonance imaging (MRI) in people with aMCI. Specifically, we aim to:**1A:** Estimate effect sizes for changes in cerebral perfusion and functional connectivity in the different treatment groups. We hypothesize that there will be preliminary evidence for improved functional connectivity in the computerized cognitive training group compared to the other two groups and that there will be changes in the cerebral perfusion as a result of yoga.**1B:** Estimate the relationships between changes in cerebral perfusion and functional connectivity, cognitive function, daily function, mood, anxiety, and quality of life within the two experimental groups compared to the control group. We hypothesize that improvement in cerebral perfusion and functional connectivity will be associated with improvement in cognitive functions, daily function, mood, anxiety, and quality of life in the individuals with MCI. Furthermore, we hypothesize that these changes are associated with an improvement in mood, anxiety, quality of life, and caregiver burden.**1C:** Establish recruitment and retention rates for this trial design.

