#### MRI acquisitions

All images will be acquired using a 3-T MRI scanner (Siemens Prisma) that is controlled for quality and are monitored weekly. We will use imaging to assess the efficacy and to elucidate the mechanisms of intervention impact by measuring brain changes over the intervention period. The primary imaging outcomes will be structural MRI (sMRI), arterial spin labeling (ASL), and resting state fMRI. Diffusion tensor imaging (DTI) will also be acquired. In addition, we will also ascertain the degree of vascular pathology using fluid-attenuated inversion recovery (FLAIR) and susceptibility-weighted MRI. The detailed imaging protocol and imaging measures are described in the supplementary neuroimaging protocol, which can be found in Additional file 1.

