### Statistical methods

The primary analyses will use linear mixed effects models to examine change from baseline to post intervention (~ 6 months) in each of the outcomes. These models control for within-subject effects through the use of per-subject random effects for slopes and intercepts over the six-month follow-up period. We will estimate the degree of change over time in each of the specific measurement intervals within randomized groups and test for differences in these changes between groups while conforming to linear model assumptions. We will evaluate the assumptions required for the appropriate use of linear models and will apply any needed transformations in the data to conform to the model assumptions. Analyses will be conducted to assess the aims listed above. In addition, to make it possible to identify which individuals are most likely to benefit from the interventions, we will incorporate variables to evaluate whether variables either attenuate or modify cognitive or imaging changes. Additional analyses are currently unknown. Missing data will be handled based on what appears to be most appropriate for the analysis being conducted. No interim analyses will be conducted.

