## Discussion

Computerized cognitive training and increased physical activity have shown to be amongst the most promising interventions in individuals with aMCI. However, the neural mechanisms underlying these interventions are currently unclear. The aim of this pilot trial is to study the feasibility of an investigation of the neuroimaging impact of computerized cognitive training versus yoga versus an active control intervention, as part of a multi-component treatment program, in persons with aMCI. Strengths of the current trial include the multicomponent design, which allows us to compare treatments while all participants received an intervention. The limitations of the current trial include our inability to blind participants to their experimental condition, possibly biasing results. Our Treatment Diffusion log was developed to control for this bias. The current trial will lay the groundwork for a larger study examining the impact of computerized cognitive training, yoga, and an active control intervention (wellness education) on changes in cerebral perfusion and functional connectivity as well as cognition, daily functioning, mood, anxiety, and quality of life in individuals with aMCI. The pilot trial will be conducted and reported in accordance with the Consolidated Standards of Reporting Trials (CONSORT) and the Standard Protocol Items: Recommendations for Interventional Trials (SPIRIT) guidelines. In Additional file 2, the SPIRIT 2013 Checklist is provided. In Additional file 3 and 4, the CONSORT 2010 guidelines checklists for reporting a pilot or feasibility trial and for journal or conference abstracts are provided.

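### The pilot aims at feasibility and effect-size estimation, but between arms its primary analysis only tests, with low power at 25 per arm

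*Protocol article*

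**What the plan says.** **Objectives.** The abstract (Methods) states: "The objective of the current pilot study is to explore the feasibility of a trial". It continues: "We will establish preliminary effect sizes regarding the association of each intervention with neuroimaging and cognitive and participant-reported measures". The Discussion repeats the feasibility purpose: "The aim of this pilot trial is to study the feasibility of an investigation of the neuroimaging impact". Under Trial objectives and hypotheses, Aims 1A, 1B and 2 are worded as estimation, although they carry directional hypotheses. Aim 1C, which stands among the primary aims, is: "Establish recruitment and retention rates for this trial design".

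**Analysis.** The Statistical methods section defines the primary analyses as linear mixed models of change from baseline to about six months, applied to every outcome. The models estimate change within each randomized group and then "test for differences in these changes between groups while conforming to linear model assumptions". A later sentence says in general terms that the listed aims will be assessed.

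**Imaging.** The MRI acquisitions section says: "We will use imaging to assess the efficacy and to elucidate the mechanisms of intervention impact".

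**Size.** The Power and sample size paragraph under Aim 2 gives d = 0.325 for exercise and 0.327 for cognitive training. It puts the need at 118 per arm for 80% power, says group randomization may require more, and says funding limits the trial to 25 persons with aMCI per arm. The corresponding paragraph under Aim 1 gives roughly 120 per group at α = 0.05. Neither says whether the test is one- or two-sided.

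**The concern.** A pilot that sets out to learn whether a trial is feasible, and how large effects might be, should report rates and effect estimates with their uncertainty. Here the analyses labelled primary reach the between-arm comparison, where the hypotheses lie, only through a test. The MRI section's wording about efficacy points the same way.

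Followed as written, the main between-arm results would be significance tests on many cognitive, functional, mood and imaging outcomes, each with a small chance of detecting the effect the protocol has in mind. A null result could be taken as no effect, and a chance positive as efficacy. Neither helps to plan the larger trial. In addition, recruitment and retention have no baseline value and no change within a person, so the model described for each outcome cannot produce the quantities in Aim 1C.

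**Working it through.** **Inputs.** From the protocol article: d = 0.325, taken as a difference between two independent means as the article's own calculation does; α = 0.05; 80% power; 118 per arm; 25 per arm available; nine sessions, so three per arm with 25/3 = 8.33 dyads each. Assumed, because the article gives no value: an intraclass correlation (ICC) by session of 0 to 0.10.

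**1. Reproduce 118 per arm.** n = 2(z_α + z_β)²/d², with d² = 0.1056 and z_β = 0.842.
- One-sided 5%: 2 × (1.645 + 0.842)²/0.1056 gives 118 after rounding up. The t-based calculation gives 117.7.
- Two-sided 5%: 2 × (1.960 + 0.842)²/0.1056 gives 149. The t-based calculation gives 149.6. Power at 118 per arm would then be 70%.

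So 118 reproduces only with a one-sided test. Power is therefore shown under both conventions.

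**2. Power at 25 per arm, ignoring sessions.** The noncentrality is d × √(n/2) = 0.325 × √12.5 = 1.149, with 48 df.
- Two-sided: 20.3%.
- One-sided: 30.4%.

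The effect detectable with 80% power, two-sided, is d = 0.81, about 2.5 times the planning value (0.81/0.325).

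**3. Power allowing for sessions.** The design effect is 1 + (8.33 − 1) × ICC, which is 1.00 at ICC 0 and 1.73 at ICC 0.10. Comparing two arms uses 3 + 3 sessions, so 6 − 2 = 4 df.

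| Assumed ICC | Design effect | Two-sided power | One-sided power |
|---|---|---|---|
| 0 | 1.00 | 14.6% | 24.7% |
| 0.02 | 1.15 | 13.3% | 22.8% |
| 0.05 | 1.37 | 12.0% | 20.6% |
| 0.10 | 1.73 | 10.5% | 18.1% |

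Power falls even at ICC 0 because the critical value now rests on 4 df.

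**4. Precision of the estimated d.** The half-width of the 95% interval is t × √(2/25) × √(design effect), with √(2/25) = 0.283.
- Ignoring sessions: 2.011 × 0.283 = 0.57.
- 4 df, ICC 0: 2.776 × 0.283 = 0.79.
- 4 df, ICC 0.10: 0.79 × √1.733 = 1.03.

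An observed difference of exactly 0.325 would have an interval that includes zero in every case. An interval shows that uncertainty; a p-value alone does not.

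**5. Aim 1C.** Retention is a share of those enrolled. With 60 of 75 retained (80%, for illustration) the exact 95% interval is 69% to 88%; with 68 of 75 (91%) it is 82% to 96%. Both ignore sessions. A mixed model of change yields neither figure.

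**The case against.** Several points on the other side are sound.

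- **The models also estimate.** The clause before the quoted words in Statistical methods says that change within arms will be estimated, and the same fitted models can supply between-arm effect sizes. A reader might infer that the primary analyses are nothing but tests; the text does not say so. What stands is narrower: between arms, the only operation named is a test.
- **Feasibility is not demoted.** Aim 1C is listed among the primary aims, and its place in the list is not a ranking. The general sentence about assessing the aims covers it nominally. How the rate is summarised is detail that an analysis plan or full protocol may hold, so its absence here is no fault in itself.
- **The shortfall is disclosed.** The article says that 118 or more per arm would be needed and that funding allows 25. It speaks of preliminary evidence and of pilot data for future studies. A reader might infer concealed low power or a plan to claim efficacy from p-values; the article supports neither.
- **A single power figure of 20% would be too firm.** It is the two-sided value. The article states no sidedness, and its own 118 implies a one-sided test, for which power is 30%.

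None of this removes the mismatch. Having acknowledged that the sample is too small, the article still places between-arm tests in the primary analyses of a study whose aims are worded as estimation.

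**Conclusion.** The point holds in limited form. The stated objectives are feasibility and effect-size estimation, while the primary analyses include between-arm tests of change in each outcome and name no between-arm estimate. Those tests have about 20% (two-sided) or 30% (one-sided) power before clustering. Allowing for sessions, power is about 15% down to 10% two-sided, or 25% down to 18% one-sided. The corresponding half-widths for d are about 0.57 ignoring sessions and about 0.8 to 1.0 with them.

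The figures that allow for sessions rest on the assumed ICC range of 0 to 0.10, equal session sizes and 4 df. All of them assume that all 25 per arm are analysed. Power is low under every convention tried, so the conclusion does not depend on which was intended.

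It does not follow that recruitment and retention should become the sole primary outcomes. Aims 1A, 1B and 2 are also stated primary aims, and replacing them would be a preference rather than a correction.

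**What to change.** 1. **Statistical methods.** Replace the words "test for differences in these changes between groups while conforming to linear model assumptions" with: *estimate between-arm differences in these changes with 95% confidence intervals that allow for session clustering; any tests are exploratory, and no efficacy conclusion will be drawn from them*.
2. **MRI acquisitions.** In the sentence "We will use imaging to assess the efficacy and to elucidate the mechanisms of intervention impact", replace the reference to assessing efficacy with *estimate preliminary effects*.
3. **Aims.** Keep Aims 1A, 1B, 1C and 2 as the primary aims. State that 1C is reported as recruitment and retention rates with confidence intervals, not through the mixed model.

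**Cost.** No new data are needed. The pilot gives up confirmatory p-values, which its size could not support. Because the trial is registered and recruiting, the change may need an amendment with IRB approval and a registry update under the article's Protocol amendments section.

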### Data monitoring

The principle investigator (PI) at each site will be responsible for monitoring the safety and efficacy of this pilot trial and executing the Data and Safety Monitoring Plan (DSMP). The DSMP will be reviewed on a monthly basis by the PI and other co-investigators as necessary.

### Harms

In this trial, we will use the Food and Drug Administration's definition of serious adverse events (SAEs) and adverse events (AEs). SAEs are unlikely in these behavioral interventions. Any SAE, whether or not it is related to the intervention, will be reported to the site Institution Review Board (IRB). The PI at each site will monitor for the presence of both SAEs and AEs at each scheduled visit. These individuals will report any SAE or AE to the overall PI twice a month. However, if the SAE involves death or a life-threatening event, the site PI will be notified within 24 h and the PI will notify the IRB within two working days from the time the SAE was first reported. Reports of SAEs received by the IRB will be reviewed by an institutional SAE board to determine the seriousness of the event and what actions, if any, will be required. In the event that a participant withdraws from the trial or the PI decides to discontinue a participant due to an SAE, the participant will be monitored by the site PI via ongoing status assessment until: (1) resolution of the problem is reached; or (2) the SAE is determined to be clearly unrelated to the trial intervention. Summary and outcome of all SAEs will be reported to the IRB annually.

### Auditing

There are no planned auditing procedures for trial conduct in place for the current trial.

### Protocol amendments

Important protocol modifications will be communicated to each of the authors and other relevant study-investigators and will be updated on ClinicalTrials.gov. IRB approval will be obtained before any important protocol modifications will be implemented. Participants will be notified should there be any important protocol modifications that would concern them.

### Confidentiality

Only the PI and Sub-Investigators that are approved by any of the three IRBs (of the University of Florida, Mayo Jacksonville, and Tallahassee Memorial Healthcare), other professionals at the study site that provide trial-related treatment or procedures, and the three IRBs are allowed to collect, use, and share protected health information. Once collected, protected health information may be shared with the study sponsor, United States governmental agencies who are responsible for overseeing research such as the Food and Drug Administration, the Department of Health and Human Services and the Office of Human Research Protections, government agencies who are responsible for overseeing public health concerns such as the Centers for Disease Control and federal, state, and local health departments, participants’ insurance companies for purposes of obtaining payment for the Support Groups and Memory Compensation components of the trial, and between the IRB-approved investigators of the other study sites (between the University of Florida, Mayo Jacksonville and Tallahassee Memorial Healthcare). Otherwise, no protected health information will be released without permission of the participant unless required by law or a court order. After the trial has been completed, protected health information will no longer be shared and used; it will be coded and will become part of a research database.

### Ancillary and post-trial care

In the event of injury as a result of study participation, the Mayo Clinic, Tallahassee Memorial Hospital, or the University of Florida will provide medical services for treatment. Such services will be provided for free if not covered by a health plan or insurance. No additional compensation will be given.

### Dissemination policy

The results will be presented at both national and international conferences and published in topline journals. Results will also be shared with participants upon request. If any questions arise regarding the data, the protocol, and the statistical codes, any of the PIs may be contacted.

## Discussion

Computerized cognitive training and increased physical activity have shown to be amongst the most promising interventions in individuals with aMCI. However, the neural mechanisms underlying these interventions are currently unclear. The aim of this pilot trial is to study the feasibility of an investigation of the neuroimaging impact of computerized cognitive training versus yoga versus an active control intervention, as part of a multi-component treatment program, in persons with aMCI. Strengths of the current trial include the multicomponent design, which allows us to compare treatments while all participants received an intervention. The limitations of the current trial include our inability to blind participants to their experimental condition, possibly biasing results. Our Treatment Diffusion log was developed to control for this bias. The current trial will lay the groundwork for a larger study examining the impact of computerized cognitive training, yoga, and an active control intervention (wellness education) on changes in cerebral perfusion and functional connectivity as well as cognition, daily functioning, mood, anxiety, and quality of life in individuals with aMCI. The pilot trial will be conducted and reported in accordance with the Consolidated Standards of Reporting Trials (CONSORT) and the Standard Protocol Items: Recommendations for Interventional Trials (SPIRIT) guidelines. In Additional file 2, the SPIRIT 2013 Checklist is provided. In Additional file 3 and 4, the CONSORT 2010 guidelines checklists for reporting a pilot or feasibility trial and for journal or conference abstracts are provided.

## Trial status

At the time of submission of this paper, patient recruitment is still ongoing.

## Abbreviations

AD QoL: Quality of Life-AD
ADLs: Activities of daily living
AE: Adverse event
aMCI: Amnestic mild cognitive impairment
BRPQ: Barriers to Research Participation Questionnaire
CCMC: Caregiving Competence and Mastery Components of the Pearlin
CDR: Clinical Dementia Rating scale
CES-D: Center for Epidemiologic Studies Depression Scale
DRS-2: Dementia Rating Scale-2
DSMP: Data and Safety Monitoring Plan
DTI: Diffusion tensor imaging
E-Cog: Everyday Cognition
FAQ: Functional Assessment Questionnaire
FLAIR: Fluid-attenuated inversion recovery
HABIT: Healthy Action to Benefit Independence and Thinking
IRB: Institution Review Board
LAR: Legally authorized representative
memSE: Self-Efficacy in Memory scale
MRI: Magnetic resonance imaging
MTT: Mirror-tracing task
PEACEOFMND: Physical Exercise And Cognitive Engagement Outcomes for Mild Neurocognitive Disorder
PI: Principle investigator
RAVLT: Rey Auditory Verbal Learning Test
REACH AIF: Anxiety Inventory Form by the Resources for Enhancing Alzheimer’s Caregiver Health project
SAE: Serious adverse event
sMRI: Structural magnetic resonance imaging
SPPB: Short physical performance battery
SRTT: Serial reaction time task
TD Log: Treatment Diffusion Log
TICS-M: Telephone Interview for Cognitive Status for Memory
WRAT4: Wide Range Achievement Test 4
WSCT: Word stem completion test
